#### Coronary computed tomography angiography with fractional flow reserve

2.9.2

CCTA images will be analyzed visually by two level three accredited CCTA readers blinded to CMR and angiographic data to determine whether the study meets criteria for FFR_CT_ analysis. The presence of coronary stenosis will be evaluated in all vessels with diameter ≥2 mm. Pseudonymized cases with ≥1 visually determined diameter stenosis of 40%–90% by either reader will be securely transferred to a central core laboratory (Heartflow Inc, Redwood City, California) for FFR_CT_ analysis with no accompanying clinical or other imaging data. A three-dimensional model will be generated from the CCTA images with computation of coronary blood flow and pressure under simulated hyperemia [38], [39]. The primary analysis will compromise images analyzable by Heartflow. Vessels with complete occlusions will be assumed to have an FFR_CT_ 0.50. Significant CAD will be determined on a per patient and vessel basis by the presence of stenosis-specific FFR_CT_ ≤0.80 2 cm distal to the location of a discrete stenosis in epicardial vessels ≥2 mm diameter.

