### Invasive coronary angiography

2.8

Coronary angiography and percutaneous coronary intervention will be performed as per routine clinical care, blinded to research imaging findings. Epicardial vessels ≥2 mm diameter with visually determined stenosis of 40%–90% will undergo FFR_inv_. A pressure sensor tipped 0.014 intra-coronary wire (PressureWire X, Abbott Vascular, Illinois, USA) will be used for hemodynamic measurements. The pressure wire will be normalized to aortic pressure at the tip of the guide catheter, and advanced beyond the stenosis being interrogated. Following intra-coronary nitrate administration, steady state hyperemia will be achieved with peripheral intravenous adenosine (140 μg/kg/min). Mean distal pressure from the pressure wire (Pd) and mean aortic pressure from the guide catheter (Pa) will be recorded. The pressure sensor will be withdrawn to the tip of the guide catheter to check for pressure drift. Adenosine infusion will then be ceased. If pressure drift is ≥5 mmHg, the FFR_inv_ measurement will be repeated. If it is <5 mmHg, Pd will be adjusted in the FFR calculation (Pd/Pa) [57].

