#### Invasive coronary angiography

2.9.3

Vessels interrogated by FFR will be interpreted by an independent observer blinded to imaging findings. An FFR ≤0.80 in an epicardial vessel ≥2 mm will be considered significant. In vessels deemed not safe to perform FFR (subtotal or complete occlusions), the vessel will be assumed to have an FFR 0.50. In vessels without FFR available, quantitative flow ratio (QFR) computation will be performed offline by an independent observer blinded to imaging and clinical details using QFR v2.2 software (Medis Medical Imaging, Leiden, the Netherlands). QFR will be performed on epicardial vessels ≥2 mm diameter with visually determined ≥25% (mild) stenosis, with QFR ≤0.80 considered significant. To perform QFR, two end-diastolic angiographic cines at least 25° apart from the vessel of interest with minimal overlap will be selected. A common reference point will be marked (typically a bifurcation or side branch) on the vessel of interest. The proximal and distal vessel will be annotated to allow automated edge detection and contouring of the vessel, which will be quality checked and manually adjusted if required. Contrast frame counting will be performed to define the start and end of contrast passage through the lesion of interest. Per-vessel QFR and maximal three-dimensional diameter stenosis will be recorded.

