The primary analysis population will comprise all patients with complete ICA and both CMR and CCTA/FFR_CT_ (excluding patients with incomplete data). Overall accuracy of CMR and CCTA/FFR_CT_ for detecting significant CAD at the patient level will be compared using the Newcombe–Wilson score method for calculating a two-sided 95% confidence interval for the difference in accuracy [62]. The primary study and substudies will be reported in accordance with the ‘Standards for Reporting Diagnostic Accuracy Studies’ (STARD) guidelines. Secondary analyses population will utilize all patients with appropriate data for each analysis. Diagnostic performance (sensitivity, specificity, predictive values) for detecting significant CAD at per patient and vessel level will be compared by using exact binomial tests and the weighted generalized score methods [63], [64]. Logistic regression models will be applied to investigate factors associated with diagnostic performance of each method, at the patient level (e.g., age, sex, pre-test probability of CAD) and vessel level (e.g., degree of stenosis, FFR); vessel-level analyses will use mixed effects regression to adjust for patient-level clustering. The overall performance of the methods will be compared, placing different weights on false positive and false negative results. Responses to questionnaires about experiences of the two scans will be summarized and compared using appropriate paired analysis methods. Similar methods will be applied for the analysis of substudies, leveraging the within-patient design to maximize power wherever possible.

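### Section 2.9.2 gives no route to a positive CCTA/FFR_CT result for a patient whose only significant lesion is a non-occlusive CT stenosis above 90%, although the reference standard does classify such vessels

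*Protocol article*

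**What the plan says.** **Index test (section 2.9.2).** Three sentences decide the CCTA/FFR_CT result.

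- Selection for FFR_CT: "cases with ≥1 visually determined diameter stenosis of 40%–90% by either reader will be securely transferred to a central core laboratory".
- Assumed values: "Vessels with complete occlusions will be assumed to have an FFR_CT_ 0.50".
- Positivity: "Significant CAD will be determined on a per patient and vessel basis by the presence of stenosis-specific FFR_CT_ ≤0.80 2 cm distal" to a discrete stenosis in a vessel of at least 2 mm.

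The same section adds: "The primary analysis will compromise images analyzable by Heartflow" (the verb is evidently meant to be comprise).

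**Reference standard (sections 2.8 and 2.9.3).** The pressure-wire range is the same: "Epicardial vessels ≥2 mm diameter with visually determined stenosis of 40%–90% will undergo FFR_inv". Two further rules cover vessels outside it. One is an assumed value: "In vessels deemed not safe to perform FFR (subtotal or complete occlusions), the vessel will be assumed to have an FFR 0.50". The other is a fallback where no FFR is available: "QFR will be performed on epicardial vessels ≥2 mm diameter with visually determined ≥25% (mild) stenosis, with QFR ≤0.80 considered significant". The fallback has no upper stenosis limit.

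**Analysis population (section 2.15).** The primary set is "all patients with complete ICA and both CMR and CCTA/FFR_CT_ (excluding patients with incomplete data").

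**The concern.** The two sides use the same 40%–90% measurement range but treat the range above 90% differently. The reference rule covers both subtotal and complete occlusions and has QFR behind it. The CT rule covers complete occlusions only and has nothing behind it.

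Read as written, the CT test can be positive at 40%–90% and at 100%, but not between those bands when that is the only lesion. This is where a test for obstructive disease should least often be negative. The article does not say whether such a patient counts as CT-negative or as incomplete.

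The primary comparison is paired and concerns overall accuracy. Qualitative CMR (section 2.9.1) is scored from perfusion and infarction with no stenosis gate, so any error from this gap falls on one test only. It shifts the estimated difference and does not cancel.

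**Working it through.** **1. The rules side by side, by severity of the patient's only lesion**

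| Lesion | CCTA/FFR_CT (2.9.2) | Reference (2.8, 2.9.3) |
|---|---|---|
| 40%–90% | sent; positive if FFR_CT ≤0.80 | FFR, or QFR if no FFR; positive if ≤0.80 |
| above 90%, not occluded | not sent; no assumed value | 0.50 if subtotal and unsafe for FFR; otherwise QFR |
| complete occlusion | 0.50 assumed, positive | 0.50 assumed, positive |

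Only the middle CT cell has no outcome.

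**2. The plan's own power figure**

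Inputs from section 2.15:
- prevalence 50%, sensitivity 85%, specificity 80% for both tests
- n = 270, margin m = 0.065, disagreement ψ = 0.10
- two-sided 95% Newcombe–Wilson interval, stated power 90%

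Accuracy of each test = 0.5 × 0.85 + 0.5 × 0.80 = 0.825.

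Paired Wald sample size = (1.960 + 1.282)² × 0.10 / 0.065² = 249. Wald power at n = 270 is Φ(0.065/√(0.10/270) − 1.960) = 92.2%. Simulating the planned paired Newcombe interval (200,000 runs) gives 90.5%. Recruitment is 270/0.9 = 300. The stated figures reproduce, so the sample size is not in error.

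**3. If the patients are scored CT-negative**

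Let s be the share of analysed patients in the gap. The documents give no value, so s is an assumption shown over a range. Assume also that these patients are reference positive, that CMR detects 85% of them (the plan's sensitivity), and that all other patients behave as planned. Then:

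- true difference (CT minus CMR): d = −0.85s
- disagreement: ψ = 0.10(1 − s) + 0.85s
- Wald power: Φ((0.065 + d)/√((ψ − d²)/270) − 1.960)

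For s = 1%: d = −0.0085 and ψ = 0.099 + 0.0085 = 0.1075.

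| s | patients in 270 | d (points) | ψ | Newcombe power | Wald power |
|---|---|---|---|---|---|
| 0 | 0 | 0 | 10.0% | 90.5% | 92.2% |
| 0.5% | 1.4 | −0.43 | 10.4% | 85.0% | 87.3% |
| 1% | 2.7 | −0.85 | 10.8% | 78.4% | 80.9% |
| 2% | 5.4 | −1.70 | 11.5% | 62.0% | 64.4% |
| 3% | 8.1 | −2.55 | 12.3% | 44.2% | 46.0% |
| 5% | 13.5 | −4.25 | 13.8% | 16.7% | 16.9% |

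**4. If they are excluded as incomplete**

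With ψ and the zero difference unchanged, Wald power is 92.2% at n = 270, 91.4% at 262 (3% lost), 90.9% at 257 (5% lost) and 90.0% at 249. The cost is not power. Patients with severe disease leave the accuracy estimate because of how CT graded them.

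**The case against.** **The group is narrow.** Transfer is per case and triggered by either reader. A patient is missed only if neither reader grades any lesion as 40%–90% and the significant lesion is above 90% without being occluded. This stands, and it is why the share is probably small. No figure in the article supports a particular value.

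**The article is a condensed document.** The full protocol or the SAP may contain the missing rule. That is possible. But section 2.9.2 does not leave the matter open: it fixes a range, an assumed value and a positivity criterion, and together these leave a hole that section 2.9.3 does not have. The point is about a stated rule, not an omitted detail.

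**The reference side has no blanket rule above 90%.** Correct. A reader might infer that every vessel above 90% is given an FFR of 0.50 at angiography. The text assigns it only to vessels unsafe for FFR because of subtotal or complete occlusion, and it does not define subtotal as 91%–99%. Other such vessels go to QFR, and their status depends on the value. The asymmetry remains, because the reference always has a rule for the vessel and CT does not.

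**Patients with no stenosis of 40% or more.** A reader might also infer that these patients drop out of the primary set because they have no FFR_CT. The text does not support this. Positivity rests on the presence of a low FFR_CT at a stenosis, so they are negative under the rule. The sentence on analyzable images follows the description of transfer and modelling, so it naturally concerns cases that were sent. Section 2.15 allows only 10% missing data, and the Background criticises earlier comparisons for being confined to CT-defined obstructive disease. A clarifying sentence is enough here.

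**CT can over-grade.** The Background notes that many lesions seen on CCTA may not cause ischemia. This stands as a modest cost of the fix.

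**Conclusion.** The point holds. As written, a patient whose only significant lesion is a non-occlusive CT stenosis above 90% cannot be CCTA/FFR_CT-positive, while the reference standard classifies the same vessel. The patient becomes a false negative or an exclusion for one of the two compared tests.

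The size is conditional. Each 1% of such patients scored CT-negative moves the expected accuracy difference by 0.85 points against CCTA/FFR_CT, out of a 6.5-point margin. The power losses in the table assume that every such patient is reference positive, that CMR sensitivity among them is 85%, and that the negative default applies. A reader might take them as the expected loss in this trial. They are not, because neither the share nor the default is given. Under exclusion, power hardly moves and the damage is to whom the accuracy estimate describes.

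It should be corrected because it concerns the definition of the primary index test. If the choice were made after the data are seen, it would be a data-dependent choice on the primary endpoint.

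**What to change.** Before database lock, reconcile sections 2.9.2, 2.9.3 and 2.15:

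- **Upper end.** Extend the assumed FFR_CT of 0.50 (positive) from complete occlusions to subtotal CT stenoses above the 90% upper limit for FFR_CT, parallel to the subtotal-or-complete convention in section 2.9.3. Define subtotal for the CT read.
- **Reader disagreement.** Say which reader's grade applies when the two differ across the 90% boundary.
- **Sensitivity analysis.** Repeat the primary comparison without the assumed values, and report how many patients they affect.
- **Clarification only.** State that cases with no stenosis of 40% or more are CT-negative and kept, and that analyzability by the core laboratory applies to cases sent.

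The cost is a few sentences and one extra analysis, using stenosis grades that the readers must already assign to select cases. The downside is that a few over-graded CT stenoses will count as positive on anatomy alone; the sensitivity analysis shows how much that matters. Section 2.16 starts analysis only after the SAP is final and the database is locked, which sets the deadline for the change.

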#### Invasive coronary angiography

2.9.3

Vessels interrogated by FFR will be interpreted by an independent observer blinded to imaging findings. An FFR ≤0.80 in an epicardial vessel ≥2 mm will be considered significant. In vessels deemed not safe to perform FFR (subtotal or complete occlusions), the vessel will be assumed to have an FFR 0.50. In vessels without FFR available, quantitative flow ratio (QFR) computation will be performed offline by an independent observer blinded to imaging and clinical details using QFR v2.2 software (Medis Medical Imaging, Leiden, the Netherlands). QFR will be performed on epicardial vessels ≥2 mm diameter with visually determined ≥25% (mild) stenosis, with QFR ≤0.80 considered significant. To perform QFR, two end-diastolic angiographic cines at least 25° apart from the vessel of interest with minimal overlap will be selected. A common reference point will be marked (typically a bifurcation or side branch) on the vessel of interest. The proximal and distal vessel will be annotated to allow automated edge detection and contouring of the vessel, which will be quality checked and manually adjusted if required. Contrast frame counting will be performed to define the start and end of contrast passage through the lesion of interest. Per-vessel QFR and maximal three-dimensional diameter stenosis will be recorded.

### Hybrid imaging strategies

2.10

CONCORD will evaluate whether hybrid imaging models improve diagnostic performance compared to single imaging approaches. Stepwise integration of anatomical information from CCTA with perfusion data from CMR may improve diagnostic accuracy by distinguishing significant epicardial CAD, CMD, or cases of dark rim artifact. Additional strategies include integration of functional data from FFR_CT_ with CMR volumetric and scar information and incorporation of CMR-derived quantitative data within the FFR_CT_ model.

### Follow-up

2.11

Follow-up of participants to identify cardiovascular outcomes (myocardial infarction, revascularization, stroke, death) at 2 years will be performed by accessing medical records through NHS electronic databases. A member of the clinical team will perform all searches of medical records. To minimize participant burden, there will be no follow-up by clinic visits, telephone, or home visits by study staff.

### Study outcomes

2.12

*Primary outcome*

The primary outcome is the diagnostic accuracy of CMR [with qualitative assessment of images] and CCTA/FFR_CT_ against the reference standard of FFR_inv_ for the detection of significant CAD at the patient level.

*Secondary outcomes*

Key secondary outcomes include the following:•Diagnostic accuracy of quantitative CMR compared with that of qualitative CMR and CCTA/FFR_CT._•Diagnostic accuracy of hybrid CMR/FFR_CT_ imaging compared with those of single modality strategies.•Clinical endpoints: all-cause mortality, subsequent percutaneous and/or surgical revascularization, myocardial infarction or stroke.

### Patient and public involvement

2.13

The design of the study and participant facing written materials (patient information leaflet and consent form) were reviewed and approved by the Leicester Biomedical Research Centre Patient Public Involvement Group who additionally gave feedback into the conduct of the study visits.

### Economic evaluation

2.14

The aim of the economic evaluation will be to determine the additional cost of CCTA/FFR_CT_, compared with CMR. The additional resource use associated with each diagnostic testing strategy will be identified, measured, and valued. This will include staff time, the cost of the scan itself (including FFR_CT_) and consumables. The additional cost of each diagnostic testing strategy will be compared with the clinical outcomes associated with each strategy. These will include the number of cases of significant CAD correctly identified, diagnostic testing time saved, and number of unnecessary angiograms avoided. The results will be presented as a cost-consequence analysis. All data on resource use and clinical outcomes will be obtained directly from the trial. Relevant unit costs will be applied to estimate the total costs for each patient with each imaging strategy.

### Statistical methods and analysis

2.15

*Sample size calculation*

For sample size calculation, we assume a CAD prevalence of 50% and that qualitative CMR and CCTA/FFR_CT_ will both achieve 85% sensitivity and 80% specificity, whereas quantitative CMR will achieve 90% sensitivity and specificity. The diagnostic accuracy of CCTA/FFR_CT_, qualitative CMR, and quantitative CMR in the whole population will be compared, with the sensitivity and specificity of the three tests compared as secondary analyses. For the primary outcome, with 270 patients undergoing each test, the study will have 90% power to show non-inferiority of CCTA/FFR_CT_ to qualitative CMR at the patient level within a non-inferiority limit of 6.5%, assuming that the two tests disagree no more than 10% of the time [14]. For the secondary outcomes, this sample size will also afford 90% power to demonstrate superiority of quantitative CMR over qualitative CMR and CCTA/FFR_CT_, assuming disagreement is no more than 14%. To allow for missing or incomplete data in up to 10% of participants, 300 patients will be recruited.

*Statistical analysis*

The primary analysis population will comprise all patients with complete ICA and both CMR and CCTA/FFR_CT_ (excluding patients with incomplete data). Overall accuracy of CMR and CCTA/FFR_CT_ for detecting significant CAD at the patient level will be compared using the Newcombe–Wilson score method for calculating a two-sided 95% confidence interval for the difference in accuracy [62]. The primary study and substudies will be reported in accordance with the ‘Standards for Reporting Diagnostic Accuracy Studies’ (STARD) guidelines. Secondary analyses population will utilize all patients with appropriate data for each analysis. Diagnostic performance (sensitivity, specificity, predictive values) for detecting significant CAD at per patient and vessel level will be compared by using exact binomial tests and the weighted generalized score methods [63], [64]. Logistic regression models will be applied to investigate factors associated with diagnostic performance of each method, at the patient level (e.g., age, sex, pre-test probability of CAD) and vessel level (e.g., degree of stenosis, FFR); vessel-level analyses will use mixed effects regression to adjust for patient-level clustering. The overall performance of the methods will be compared, placing different weights on false positive and false negative results. Responses to questionnaires about experiences of the two scans will be summarized and compared using appropriate paired analysis methods. Similar methods will be applied for the analysis of substudies, leveraging the within-patient design to maximize power wherever possible.

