## Background

1

Coronary artery disease (CAD) remains a leading cause of morbidity and mortality worldwide [1]. Despite advances in pharmacological therapy and revascularization techniques, the optimum diagnostic algorithm remains uncertain. Invasive coronary angiography (ICA) remains constrained by its high cost, attendant risks, and low diagnostic yield when utilized first-line [2], [3], with fewer than half of patients requiring follow-on revascularization [4]. International guidelines recommend non-invasive imaging as a “gatekeeper”, to refine diagnosis and improve the targeting of invasive procedures [5], [6]. Favorable diagnostic and prognostic capabilities have been established for a variety of non-invasive imaging modalities in patients with suspected CAD [7], [8], [9], [10], [11].

Cardiovascular magnetic resonance (CMR) offers excellent diagnostic accuracy to detect ischemia [12], [13], [14], [15], [16], with proven utility in reducing unnecessary invasive procedures and providing accurate prognostic information [17], [18], [19], [20], [21]. Furthermore, the contemporaneous volumetric and scar assessment provided by CMR enables the identification of viable myocardium and improves diagnostic confidence in detecting obstructive disease [22], [23], [24], [25].

Coronary computed tomography angiography (CCTA) is an accurate diagnostic test in patients at a low-intermediate risk of CAD [6]. CCTA affords high sensitivity and negative predictive value, allowing the safe exclusion of obstructive CAD, obviating the need for further investigations, while conferring an excellent prognosis [26], [27], [28], [29], [30], [31]. Furthermore, CCTA in addition to standard care reduces cardiovascular death and non-fatal myocardial infarction, owing to the identification of non-obstructive CAD which may be targeted by disease-modifying pharmacotherapies [32]. In the United Kingdom (UK), the National Institute for Health and Care Excellence recommends CCTA as the preferred first-line test in all patients without known CAD presenting with stable chest pain [33].

However, the accuracy of CCTA may fall in patients with higher pre-test probability of disease or those with known CAD. Moreover, a large proportion of CCTA-identified lesions may not cause ischemia [34], [35], [36], which in turn may lead to increased rates of ICA and revascularization, without necessarily improving clinical outcome [37].

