### Study objectives

1.1

The primary objective is to determine whether, in patients with suspected angina referred for ICA, the diagnostic accuracy of CCTA/FFR_CT_ is non-inferior to that of qualitatively assessed stress-perfusion CMR to detect obstructive CAD. Secondary objectives include determining whether (1) quantitative stress-perfusion CMR affords superior diagnostic accuracy compared with qualitative CMR and CCTA/FFR_CT_, (2) hybrid imaging models outperform single modality strategies, (3) CMR/CCTA imaging parameters predict major adverse cardiovascular events (MACE).

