#### Cardiovascular magnetic resonance

2.9.1

CMR images will be analyzed offline, blinded to participant and angiographic details using cvi42 software (Circle Cardiovascular Imaging, Calgary, Canada). Image quality will be graded on a 4-point Likert scale: 3=excellent, 2=good, 1=moderate, and 0=unanalyzable. For volumetric assessment, the built-in automated contouring tool will define endocardial and epicardial borders in the end-diastolic and end-systolic phases of the short-axis stack (smooth segmentation with exclusion of papillary muscles and trabeculations), with manual adjustments made for clear and obvious errors. Qualitative interpretation of exams will be performed by two experienced level three CMR accredited cardiologists acting in consensus following two independent reads with assessment of resting wall motion, LGE, and perfusion. A third reader will adjudicate in cases of unresolved consensus. Findings will be reported using the 16-segment American Heart Association (AHA) model [58], and further subdivided into subepicardial and subendocardial layers for perfusion and LGE assessment (32-segment model). Myocardial segments are ascribed a coronary artery territory according to standard criteria [58]. For resting wall motion assessment, standard segmental scoring will be performed: 1=normal, 2=hypokinesia, 3=akinesia, 4=dyskinesia, 5=aneurysmal [59]. For qualitative LGE assessment, scar will be graded at a segmental level: 0=normal, 1=subendocardial, 2=transmural, 3=non-ischemic, 4=insertion point fibrosis.

For quantitative LGE assessment, the full width at half maximum technique will be used. A region of interest will be drawn around an area of hyperintense myocardium on a single slice to define the maximal signal, with infarct defined as myocardium with >50% the peak signal intensity of the infarct core [60]. Exclusion zones will be applied to non-infarct territories or areas with erroneous signal detection. Total enhanced mass will be calculated and expressed as a percentage of total myocardial mass. For T1 mapping analysis, the built-in automated contouring tool will define endocardial and epicardial borders, with a 10% offset applied to each border to minimize the risk of blood pool inclusion or partial volume effects.

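### The primary comparison covers only patients in whom both tests gave a usable result, while the conclusion is drawn for all patients referred for ICA

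*Protocol article*

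**What the plan says.** The primary objective (section 1.1) is whether, in patients with suspected angina referred for ICA, the accuracy of CCTA/FFR_CT "is non-inferior to that of qualitatively assessed stress-perfusion CMR to detect obstructive CAD". The Summary (section 4) says that confirming this would support wide adoption of CCTA/FFR_CT in patients at moderate-to-high risk.

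The set analysed is narrower. Section 2.15 states: "The primary analysis population will comprise all patients with complete ICA and both CMR and CCTA/FFR_CT_ (excluding patients with incomplete data"). Section 2.9.2 adds: "The primary analysis will compromise images analyzable by Heartflow", where the verb is evidently meant to be 'comprise'. For CMR, section 2.9.1 says: "Image quality will be graded on a 4-point Likert scale: 3=excellent, 2=good, 1=moderate, and 0=unanalyzable". It does not say what result a grade 0 scan receives. I infer from the incomplete-data exclusion that such a patient is dropped.

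The sample size paragraph of section 2.15 states that "with 270 patients undergoing each test, the study will have 90% power" to show non-inferiority "within a non-inferiority limit of 6.5"%, and then: "To allow for missing or incomplete data in up to 10% of participants, 300 patients will be recruited". Secondary analyses use all patients with appropriate data for each analysis, which does not count a failed scan as a failure either.

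**The concern.** A scan that cannot be analysed is a result of the testing strategy. A clinician who orders the test meets that result and has to act on it. Dropping these patients turns the question from how accurate each test is in referred patients into how accurate each is when both happen to work.

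In a non-inferiority comparison this matters in one direction. If the new test fails more often than the comparator, removing its failures makes it look closer to the comparator than it is across all referred patients. Non-inferiority could then be declared and carried over to a population in which a wider gap exists. This is a rule that the article states, not a detail left open, so an analysis plan that follows the article inherits it.

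**Working it through.** **Inputs from section 2.15.** Prevalence 50%; sensitivity 85% and specificity 80% for both tests; disagreement at most 10%; margin 6.5 points; two-sided 95% Newcombe-Wilson interval; 270 analysed, 300 recruited.

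**The plan's own figures.** Accuracy = 0.5 × 0.85 + 0.5 × 0.80 = 0.825 for each test, so the planned true difference is 0. Simulating the paired Newcombe interval with n = 270, accuracy 0.825 for each test and 10% disagreement gives power of 90.5%, against the stated 90%. Recruitment: 270 / 0.90 = 300. Both reproduce, so the sample size is not in question.

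**Assumptions.** The article gives no non-analysable rate. I let a fraction f of CCTA/FFR_CT scans fail, let CMR never fail, and keep both accuracies at 0.825 when analysable. This is one side of the possible range.

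**Shift in the all-patient difference (CCTA/FFR_CT minus CMR).** With q the proportion of failed scans counted as correct:

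shift = f × (q − 0.825)

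- Counted as test-positive, with an assumed 60% prevalence among failures: q = 0.60, so shift = −0.225 × f. Taking CMR accuracy at that prevalence instead, 0.6 × 0.85 + 0.4 × 0.80 = 0.83, gives −0.23 × f, which is nearly the same.
- Counted as incorrect (worst case): q = 0, so shift = −0.825 × f.

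| f | test-positive, 60% prevalence | incorrect (worst case) |
|---|---|---|
| 5% | −1.1 points | −4.1 points |
| 8% | −1.8 points | −6.6 points |
| 10% | −2.25 (about −2.3) points | −8.25 (about −8.3) points |

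In the worst case the whole margin is used when f = 0.065 / 0.825 = 7.9%. Under the test-positive rule that would take f = 0.065 / 0.225 = 29%.

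**Probability of declaring non-inferiority, same interval, simulated.**

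| f | complete cases | all 300, test-positive | all 300, incorrect |
|---|---|---|---|
| 5% | 92% | about 75% | about 20% |
| 8% | 91% | about 61% | about 2% |
| 10% | 90% | about 50% | about 0.4% |

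The complete-case result hardly responds to f, because the failed scans have left the data.

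**Other directions.** If both tests fail in 5%, independently of disease and of each other, and failures count as incorrect, each accuracy is 0.95 × 0.825 = 0.784 and the difference stays 0. If CMR fails more often, the signs above reverse and the complete-case set works against CCTA/FFR_CT.

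**The case against.** The strongest reply is that accuracy in patients with both tests is a legitimate target and the one that the study is powered for. Under that target the planned test behaves as intended. This stands. If the all-patient difference is set at exactly −6.5 points with failures counted as incorrect, the complete-case rule declares non-inferiority about 55% of the time at f = 5% and 92% at f = 8%. A reader might infer that the 2.5% error rate is inflated to those levels. It is not: at f = 8% the complete-case difference is (−0.065 + 0.825 × 0.08) / 0.92 = +0.1 points, so the claim is true for the patients analysed. The figures show a gap between two targets. Under the test-positive rule the corresponding rates are about 7% at 5% failures and 15% at 10%.

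Three other strong readings are also unsupported:

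- That CCTA/FFR_CT will fail more often. No section says so. The Background remark that "the accuracy of CCTA may fall in patients with higher pre-test probability of disease or those with known CAD" concerns accuracy, which a complete-case analysis would capture, and not scan failure. FFR_CT is requested only where a reader sees a 40% to 90% stenosis, so core-laboratory failure can arise only in that subset.
- That the plan expects 10% CCTA/FFR_CT failure. The 10% allowance covers missing or incomplete data of every kind.
- That section 2.15 promises an all-patient analysis because it speaks of accuracy in the whole population. That phrase may only distinguish overall accuracy from sensitivity and specificity. The point here rests on the objective and the Summary.

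Finally, an unseen analysis plan may contain a sensitivity analysis, and the article commits to STARD reporting. Both could soften the point. Neither changes the primary set that the article fixes, and disclosing exclusions does not change the non-inferiority decision.

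**Conclusion.** The point holds as a mismatch between the set analysed and the population of the conclusion. The primary comparison estimates accuracy when both tests work, while the objective and the Summary address all patients referred for ICA. The complete-case set favours CCTA/FFR_CT if it is non-analysable more often than CMR and disfavours it if CMR fails more. With equal failure rates, independent of disease and of the other test's result, the difference is little affected.

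The size cannot be fixed from the document. With only CCTA/FFR_CT failing, at 5% to 10%, it is about −1.1 to −2.3 points under a test-positive rule and −4.1 to −8.3 points in the worst case, against the 6.5-point margin. Only the worst-case rule takes the difference past the margin within that range. A reader might go further and call the primary analysis invalid; the documents do not support that. Severity: should-fix.

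**What to change.** Keep the complete-case analysis as primary. Before the analysis plan is finalised, prespecify a sensitivity analysis in all enrolled patients with a reference-standard result. Count non-analysable CMR and CCTA/FFR_CT scans by one rule applied alike to both tests: test-positive, with incorrect as the worst case. Use the same Newcombe interval and the −6.5% limit. Report the non-analysable rate by modality. If the two analyses disagree, limit the non-inferiority conclusion to patients with analysable scans.

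This is feasible because ICA is clinically indicated for every participant and performed blind to the research imaging (sections 2.8 and 2.16), so most patients with a failed scan should still have a reference result.

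The cost is one more analysis and possibly a narrower conclusion. Requiring success in both sets is not needed. It would cut the stated 90% power to at most about 75% at 5% CCTA/FFR_CT failures and 50% at 10%, even under the test-positive rule, and would mean revisiting the 10% disagreement assumption.
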